[17], and the association of decreased light transmission by lens yellowing with sleep disturbance
[18].

The research hypothesis of the present study is that cataract surgery, which removes the clouded lens and implants an artificial intraocular lens (IOL), will increase the input of non-visual light information and improve circadian alignment and its related health outcomes, such as depression, sleep disturbances, body mass regulation, and glucose and lipid metabolism
[19].

The hypothesis is supported by studies of bright light intervention and light exposure in real-life situations. A Cochrane systematic review showed a significant reduction of depressive symptoms (standardised mean difference −0.20, 95% CI −0.38 to −0.01) from a meta-analysis of 18 randomized controlled trials (RCTs) among 505 patients with non-seasonal depression
[20], and another systematic review also revealed the significant effectiveness of bright light intervention and light exposure among seasonal affective disorders (eight RCTs totalling 132 patients)
[21]. In addition, recent RCTs have revealed the effectiveness of bright light therapy on depression, accompanied by improved sleep quality and internal biological rhythm. Bright light therapy (pale blue light at 7,500 lux for one hour) significantly decreased depressive symptoms compared with the placebo control group (red dim light at 50 lux) among 89 patients with non-seasonal depression, and was accompanied by an increase in salivary melatonin in the evening and better actigraph-measured sleep parameters
[22, 23]. An intervention to increase light exposure by installing a ceiling light in the shared living room in group care facilities significantly decreased depressive symptoms, and increased total sleep time, as assessed by an actigraph, among elderly participants. In addition, a significant interaction of light intervention and melatonin administration on sleep efficiency was observed
[24]. Higher daylight exposure increases melatonin secretion at night, according to an interventional study
[25] and our population-based observational study
[26].

Short-term and long-term influence of cataract surgery on depression and subjective sleep quality have been reported by some observational studies. Compared with depressive symptoms assessed before cataract surgery, significant decreases in depressive symptoms have reported at two months
[27, 28], three months
[29], and one year

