### Primary outcome

We will assess depressive symptoms as a primary outcome of the present study using the short version geriatric depression scale GDS-15. Prevalence of depression, median of GDS-15, and the mean value of difference between baseline and three months later will be compared between the intervention group and the control group.

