### Sample size

According to the HEIJO-KYO study
[26], a community-based cohort study among the elderly (mean age ± standard deviation: 72 ± 7.1) in the same district as the present study, the prevalence of depression was 20.0% (101 out of 506)
[37]. To detect its 7% difference as significant at a two-sided α level of 5% with a power of 80%, it was calculated that 475 participants in each group would be required. Assuming a dropout of 5%, we estimated that a total of 1,000 participants would be needed.

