### Statistical analysis

We will compare the outcomes between the control group and the intervention group based on the intention-to-treat principle. For missing values due to loss to follow-up after baseline measurement, we will impute baseline data using the last observation carried forward (LOCF) method. For continuous variables with normal distributions, the mean and standard deviation will be reported. For variables not distributed normally, the median and interquartile range will be reported. Means, medians, and proportions will be compared using the t test, the Mann-Whitney U test, and the χ^2^ test, respectively. We will use analysis of covariance to estimate adjusted mean values and 95% CIs. The prevalence of the two groups will be tested using multivariate logistic regression analysis. To assess the phase, amplitude, and robustness of the circadian rhythm, we will use the cosinor model
[69], the sigmoidally transformed cosine model
[70], and the generalised additive model
[71]. We will conduct a subgroup analysis at baseline according to the severity of cataract and chronotype.

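### The tests named for GDS-15 ignore the baseline score or use raw change, and no planned adjusted model names baseline GDS-15: an avoidable loss of efficiency

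*Protocol article*

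**What the plan says.** Under Primary outcome, GDS-15 is to be compared in three forms: prevalence of depression, the median score, and a change score ("the mean value of difference between baseline and three months later will be compared").

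Under Statistical analysis, the tests follow the type of summary: "Means, medians, and proportions will be compared using the t test, the Mann-Whitney U test", and the chi-square test for proportions. The next two sentences add analysis of covariance for adjusted means with 95% CIs, and multivariate logistic regression to test prevalence. Neither sentence lists covariates, and nothing ranks the adjusted models above or below the simple tests.

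The Abstract and the Discussion name day length at outcome measurement as an adjustment variable. The Discussion gives it as an example of a seasonal variable and calls the continuous-outcome method ANOVA, whereas Statistical analysis calls it analysis of covariance. Baseline GDS-15 is not named as a covariate anywhere.

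Under Sample size, the trial is sized on the dichotomised score alone: "the prevalence of depression was 20.0% (101 out of 506") in a local cohort, a 7-point difference is targeted, and "it was calculated that 475 participants in each group would be required".

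**The concern.** The baseline value of an outcome is usually its strongest predictor, and here it is already collected. A follow-up-only comparison leaves the predictable part of the between-person variation in the error term. A raw change score removes it by subtracting the whole baseline, which over-corrects whenever the correlation between visits is below 1. ANCOVA estimates how much of the baseline to subtract.

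As the text stands, the result for GDS-15 could rest on an unadjusted chi-square, Mann-Whitney or change-score t test. The adjusted models could also be run with day length alone. Either course gives wider intervals than the collected data allow. The same applies to continuous secondary outcomes measured at baseline.

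**Working it through.** **Inputs from the Sample size section.** Control prevalence 0.20 (101/506 = 0.1996); a 7-point difference, read as 20% versus 13%; two-sided α 5%; power 80%; 475 per group; 5% dropout. Allocation is 1:1 (Methods/Design).

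**Inputs not in the document.** The SD of GDS-15 and its correlation r between baseline and follow-up. I assume r = 0.3, 0.5 and 0.7, equal variance at both visits, and a normal score. Power is by normal approximation.

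**Step 1: the plan's own figure.** Pooled formula without continuity correction:

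n = [1.960·√(2·0.165·0.835) + 0.842·√(0.20·0.80 + 0.13·0.87)]² / 0.07² = 440.2, so 441.

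With continuity correction it is 469, which is 1.3% below the stated 475. Dropout: 475/0.95 = 500 per group, 1,000 in total, as stated. Uncorrected power at 475 per group:

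Φ[(0.07·√475 − 1.960·√0.2756) / √0.2731] = Φ(0.95) = 0.829.

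The stated target is met.

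**Step 2: relative variance.** With the follow-up score's variance set to 1, raw change has 2(1 − r) and ANCOVA has 1 − r². The ratio of ANCOVA to raw change is (1 − r²)/[2(1 − r)] = (1 + r)/2.

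| r | Follow-up | Raw change | ANCOVA | Saving vs follow-up | Saving vs change |
|---|---|---|---|---|---|
| 0.3 | 1 | 1.40 | 0.91 | 9% | 35% |
| 0.5 | 1 | 1.00 | 0.75 | 25% | 25% |
| 0.7 | 1 | 0.60 | 0.51 | 49% | 15% |

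For every r strictly between 0 and 1, ANCOVA has the smallest variance of the three.

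**Step 3: power at an illustrative standardised difference of 0.20.** This size is that of the light-therapy meta-analysis cited in Background ("A Cochrane systematic review showed a significant reduction of depressive symptoms"; standardised mean difference −0.20, 95% CI −0.38 to −0.01). It serves as a benchmark only. At 475 per group, power = Φ(0.20·√(475/2)/s − 1.96) = Φ(3.082/s − 1.96), where s is the square root of the relative variance.

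| r | Follow-up t test | Raw-change t test | ANCOVA | Gain over follow-up | Gain over change |
|---|---|---|---|---|---|
| 0.3 | 87% | 74% | 90% | 3 points | 16 points |
| 0.5 | 87% | 87% | 94.5% | 8 points | 8 points |
| 0.7 | 87% | 98% | 99% | 12 points | 1 point |

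**Step 4: separate the effect of dichotomising.** On the same normal score, a shift of 0.20 SD moves prevalence from 20% to Φ(−0.8416 − 0.20) = 14.9%, and power on prevalence is 55%. Going from 55% to 87% on the unadjusted follow-up score is 32 points, gained before any baseline value is used. Baseline adjustment then adds the 3 to 12 points above.

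**Step 5: the same comparison at the design effect.** 20% versus 13% is a shift of z(0.87) − z(0.80) = 0.285 SD on a normal score. At 475 per group:

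- chi-square: 83%
- follow-up t test: 99.2%
- raw change: 96.0%, 99.2% and above 99.9% at r = 0.3, 0.5 and 0.7
- ANCOVA: 99.6%, 99.9% and above 99.9%

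ANCOVA therefore adds less than 1 point over follow-up only and at most about 4 over raw change, because score-based power is already near its ceiling. For prevalence, logistic regression with the baseline score as covariate reached 87%, 89% and 93% at r = 0.5, 0.6 and 0.7, against 82% to 83% for chi-square (simulation on a normal score, 1,500 trials per r).

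**The case against.** The strongest reply is that adjusted models are already planned. Directly after the simple tests come ANCOVA and a logistic regression that is to test prevalence, and the Discussion treats adjustment as part of the comparison. Day length is introduced as an example, nothing rules out baseline GDS-15, and an article may leave a covariate list to a fuller document.

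Much of this stands. A reader might infer that the plan has only unadjusted tests, or that it calls them primary. Neither is so: both adjusted models are stated, and no test is labelled primary. An incomplete covariate list would not by itself be a finding. What remains is that the article does state, for each form of the primary outcome, a test that ignores baseline or uses raw change, and does not put the adjusted models ahead of those tests. The one adjustment purpose it describes is season, which baseline GDS-15 does not serve.

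The second reply is that the trial is adequately powered for its own target. That is correct. A reader might infer from the 55% in Step 4 that the trial is close to a coin-flip. The documents do not support this. The plan never adopts 0.20 as its effect; it is background evidence on light therapy in patients with non-seasonal depression, whereas this trial tests surgery and excludes major depression under current therapy. The whole gap between 55% and the ANCOVA figures should not be credited to baseline adjustment either, since most of it comes from dichotomising. The plan already compares the score itself in two of its three forms.

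**Conclusion.** The point holds as one of efficiency, not of validity or of a wrong sample size. The tests named for GDS-15 do not use baseline well, and the planned adjusted models neither name it nor are made the main analysis.

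That ANCOVA has lower variance than both alternatives follows for any r between 0 and 1 with equal variances at the two visits. How much lower depends on r, which the documents do not give. The power gains also rest on a normal score and on the chosen effect: worthwhile at 0.20 SD, small at the 0.285 SD equivalent of the design target. GDS-15 is a 15-item score and may well be skewed, so the power figures are a guide, not a forecast.

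**What to change.** In Statistical analysis:

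1. Make ANCOVA of follow-up GDS-15 on arm, baseline GDS-15 and day length, with robust standard errors, the main analysis of the score. It replaces the unadjusted t and Mann-Whitney tests; medians can still be reported descriptively.
2. Name baseline GDS-15 and day length as covariates in the logistic regression already planned for prevalence, and make that model the test in place of chi-square.
3. Apply the same baseline adjustment to continuous secondary outcomes measured at baseline, such as PSQI, HbA1c and BMI.
4. Use one name, ANCOVA, in both Statistical analysis and Discussion.

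Keep the total of 1,000 and the stated prevalence-based power. Day length should stay in the model, because the Discussion relies on it to handle the unequal time to follow-up. Which of the three GDS-15 forms is the single primary comparison is a separate decision that this change does not settle.

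The cost is one more model term and a reworded section. No new data, visits or participants are needed, and the article states that recruitment had not begun.

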## Discussion

To conduct an RCT assessing the long-term effect of cataract surgery is ethically difficult, because the effectiveness of cataract surgery for visual acuity is established. To assess the effect of cataract surgery after three months with minimum disadvantage to the control group due to delayed surgery, we have potential limitations due to the difference of duration from baseline survey to outcome measurements between the two groups. Compared with the control group, the intervention group will spend a longer time from baseline measurement to outcome measurement due to the duration between baseline and surgery, and it may distort the results because of a seasonal effect on outcomes. However, we will continuously include participants with a similar speed though the year, and will finish this study at the same date as started in the previous year. As a result, the number of overestimated outcomes and underestimated outcomes due to the seasonal influence will be balanced between the two groups. In the statistical analysis, we will compare the outcomes adjusted for seasonal variables, such as day length at outcome measurement, using ANOVA for continuous variables and multivariate logistic regression analysis for categorical outcomes.

## Trial status

At the time of submission, the study protocol has been fixed and registered for clinical trial registration, but the recruitment of participants has not started. Recruitment of participants is expected to begin August 2014.

## Abbreviations

aMT6-s: 6-sulfatoxymelatonin
BMI: Body mass index
FPG: Fasting plasma glucose
GDS-15: The short version geriatric depression scale
HDL-C: High-density lipoprotein cholesterol
IOL: Intraocular lens
ipRGCs: Intrinsically photosensitive retinal ganglion cells
LDL-C: Low-density lipoprotein cholesterol
PIPR: post-illumination pupil response
RCTs: Randomized controlled trials
SCN: Suprachiasmatic nuclei
TG: Triglyceride.
